#### Analysis plan

This trial addresses two different questions separated by primary aim and secondary aim: 1) Is ASAP superior to DEUCC (primary aim)?, and 2) Is ASAP or DEUCC superior to UCC, (secondary aim) For all analyses, assumptions required for the data distribution (e.g., normal distribution) will be assessed. Any transformations of data or alternative methods necessary to analyze the data will be determined by examining the structure of the data. All analyses will be performed in accord with the intent-to-treat (ITT) principle (e.g., group status is determined by randomization at baseline). A p-value < 0.05 will be used to indicate statistical significance for all analyses.

The primary aim analyses will compare the ASAP and DEUCC group change in log WMFT time score and success rate from the SIS hand domain and the full SIS. For the primary hypothesis, change in WMFT time score at 1 year, an independent sample t-test will be used to compare the mean change in log-transformed WMFT time score, and analysis of covariance (ANCOVA) will be used to adjust for *a priori* covariates (site, initial motor impairment, stroke duration to randomization, baseline log time score) and any baseline variables that were imbalanced between ASAP and DEUCC. For missing data from loss to follow-up or missed evaluations at 12-months, multiple imputation using all available evaluation data will be utilized. Adjusted least-square means and the associated 95% confidence interval will be presented as well as p-value, and effect sizes will be computed to aid in interpretation of results.

For the secondary hypothesis, the success rate of the SIS hand domain will be calculated as the percent of subjects in the ASAP and DEUCC groups that achieved at least a 25-point increase in normalized SIS hand function at 1 year post randomization compared to baseline. Logistic regression will be used to compare these rates between groups, while adjusting for covariates. Since there are no prior data or biological evidence suggesting that ASAP will have a differential effect on one subgroup compared to DEUCC in the targeted population, we are not planning any *a priori* interactions between treatment and any of the covariates in the main analysis. However, we will perform exploratory data analysis to examine these possible interactions and generate hypotheses for future studies.

The analytic approach to the secondary aims will follow that described for the primary aims above, with the exception of comparing differences between groups receiving 30 hours of treatment (ASAP and DEUCC) to UCC. For other secondary outcomes, baseline to 1-yr change will be compared between ASAP and DEUCC groups and ASAP and UCC groups using analysis of covariance or logistic regression models (see Additional file 1). In addition, a composite physical domain, which includes strength, hand function, ADL/IADL, and mobility, will be created and compared in a similar way. Bonferroni adjustments will be made of the critical p-value for these secondary analyses, as there are two comparisons: ASAP to UCC and DEUCC to UCC; a p-value < 0.025 will be used to indicate significance.

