### Statistical analysis

#### Sample size and participant accrual

Sample size estimates were computed for the primary *a priori* aim of detecting a clinically relevant difference in log-transformed WMFT time score between ASAP and DEUCC at 1 year follow up with α = 0.05. With the proposed total sample of 360, we would have sufficient power to detect a moderate difference in treatment effect of Δ = 0.40 for an attrition rate of 17%, and Δ = 0.42 for an attrition rate of 25% using a two-group 2-sided t-test with a type I error of 0.05 and 80% power. The EXCITE trial showed treatment effect sizes of 0.50 and 0.63 for the high and low functioning groups, respectively. For the small sample phase II VECTORS study, a similar analysis showed a treatment effect size of 0.20. Given the outpatient timing of ICARE, a less dynamic period of change than VECTORS, we expect to have sufficient power to detect the effect size in log WMFT time score. We also should have sufficient power to detect a difference in the proportion of participants who change ≥ 25 points on the normalized SIS at 1 year using a χ^2^ statistic. The minimal success rate difference that can be detected with 80% power ranges from 13.5-20% (with 17% attrition) to 14.0-21% (with 25% attrition); the variation in the estimates reflects potential variation in improvement in the DEUCC group. To achieve this recruitment goal (N = 360) in 40 months, each of the three centers aims to randomize 3 participants per month.

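### The 25-point SIS-hand success rule has no provision for baselines above 75, gives up power by dichotomising, and is not paired with a continuous analysis or a named baseline SIS-hand covariate

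*Protocol article*

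**What the plan says.** The SIS hand domain and the full SIS are the secondary outcomes, and the secondary hypotheses for all three pairwise comparisons are worded as proportions of patients with success.

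- **Definition.** Under Analysis plan, a hand-domain success is a participant who "achieved at least a 25-point increase in normalized SIS hand function at 1 year post randomization compared to baseline". No other route to success is given.
- **Model.** The success rates are compared by logistic regression with covariate adjustment, but that sentence lists no covariates. The only a priori list stands in the preceding paragraph, for the ANCOVA of log WMFT time: "covariates (site, initial motor impairment, stroke duration to randomization, baseline log time score". The Baseline section adds any characteristic found to differ between groups.
- **Power.** Sample size and participant accrual gives detectable effects for both types of outcome. For log WMFT time they are "Δ = 0.40 for an attrition rate of 17%, and Δ = 0.42 for an attrition rate of 25" per cent. For SIS success, "The minimal success rate difference that can be detected with 80% power ranges from 13.5-20% (with 17% attrition) to 14.0-21% (with 25% attrition"), where "the variation in the estimates reflects potential variation in improvement in the DEUCC group". No DEUCC success rate is printed.
- **Population.** Fugl-Meyer scores from 19 to 58 are eligible. The printed (truncated) criteria set no upper limit on SIS-hand.

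**The concern.** A fixed gain on a bounded scale cannot be reached by those who start near the top. On a 0-100 scale the largest possible gain is 100 minus baseline, so a participant who goes from 80 to 100 is scored a failure alongside one who did not improve. The trial enrols mild to moderate impairment, so such baselines are plausible.

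Participants who cannot succeed in either arm shrink the difference in success rates. Reducing the score to yes or no also discards information from everyone else. Both effects reduce the chance of detecting a real SIS-hand benefit in any of the three comparisons, although the continuous score is collected at baseline and at 1 year. Success depends on the starting score, so one would also expect the baseline SIS-hand score to be named in the model.

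**Working it through.** **Inputs.** 360 participants in three arms; 120 per arm is inferred, since the ratio is not printed, but it reproduces the stated figures. Test: "using a two-group 2-sided t-test with a type I error of 0.05 and 80% power". Attrition of 17% leaves 120 × 0.83 = 99.6 per arm; 25% leaves 120 × 0.75 = 90.

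**Step 1: reproduce the plan's figures.**
- Continuous outcome: Δ = (1.960 + 0.842) × √(2/n). This gives 0.397 at n = 99.6 and 0.418 at n = 90 (0.399 and 0.420 with the exact t distribution). The plan says 0.40 and 0.42.
- Responder outcome: power = Φ{[d − 1.960 √(2p̄(1 − p̄)/n)] / √[(p₀(1 − p₀) + p₁(1 − p₁))/n]}, where d = p₁ − p₀ and p̄ is the mean of the two rates, solved for 80%. With p₀ = 40%, d is 19.7 points at n = 99.6 and 20.7 at n = 90. The plan's upper ends are 20 and 21.
- The lower ends, 13.5 and 14.0, arise near either extreme: p₀ of about 6-7% (13.0-13.7 points at 99-100 per arm, 13.9-14.5 at 90) or, by symmetry, p₀ of about 80% (13.4 and 14.0). The article does not say which was meant.

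The stated figures are sound.

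**Step 2: cost of dichotomising.** Assume a normally distributed score shifted by 0.40 SD and cut at a threshold, with 100 per arm. As a continuous outcome, power = Φ(0.40 × √50 − 1.960) = Φ(0.868) = 81%, and 99 per arm suffice for 80%. As a responder outcome, p₁ = Φ(Φ⁻¹(p₀) + 0.40):

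| Control success p₀ | p₁ | Power, 100 per arm | n per arm for 80% |
|---|---|---|---|
| 7% | 14.1% | 37% | 293 |
| 20% | 32.9% | 55% | 182 |
| 30% | 45.0% | 60% | 162 |
| 40% | 55.8% | 61% | 156 |
| 50% | 65.5% | 61% | 158 |

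**Step 3: cost of the ceiling.** Let f be the share starting above 75, equal in both arms. Take success rates of 40% and 59.7% among those able to succeed, which gives 80% power at 100 per arm. Both rates are then multiplied by (1 − f):

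| f | Rates | Difference | Power |
|---|---|---|---|
| 0 | 40.0% v 59.7% | 19.7 | 80% |
| 5% | 38.0% v 56.7% | 18.7 | 76% |
| 10% | 36.0% v 53.7% | 17.7 | 72% |
| 20% | 32.0% v 47.8% | 15.8 | 63% |
| 25% | 30.0% v 44.8% | 14.8 | 58% |

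The documents give no baseline SIS-hand distribution, so f is an assumption throughout.

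**Step 4: would the baseline covariate or a continuous analysis help?** Simulation with scores bounded at 0-100, 100 per arm, 1,500 runs per scenario, mean gain 22 (SD 22) and treatment effect 9 points, all assumed:

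| Baseline mean (SD) | Above 75 | Responder, unadjusted | Responder, logistic with baseline SIS-hand | Continuous ANCOVA |
|---|---|---|---|---|
| 30 (25) | 4% | 61.1% | 60.1% | 77.3% |
| 60 (25) | 27% | 40.9% | 46.5% | 68.1% |

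Adding the covariate to the logistic model changes power by about −1 to +6 points. The continuous ANCOVA adds 16 points in the first scenario (77.3 − 61.1) and 27 in the second (68.1 − 40.9).

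**The case against.** The strongest reply is that the responder outcome is deliberate. The hypotheses are stated as proportions, the threshold is fixed in advance, and its detectable differences are disclosed and reproduce. Under a definition based on improvement, a move from 80 to 100 simply is not a 25-point gain. The Analysis plan also foresees ANCOVA or logistic models for other secondary outcomes and a composite physical domain that includes hand function, so some continuous analysis touching SIS-hand may be planned. All of this stands, and it makes the point one of efficiency and interpretation. It does not supply a rule for baselines above 75, and a composite does not replace a SIS-hand analysis.

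Several stronger readings are tempting, but the documents do not support them:

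- **That SIS success is analysed without baseline SIS-hand.** The covariate list was written for the WMFT ANCOVA, the logistic sentence lists nothing, and the Baseline section would admit baseline SIS-hand if it were imbalanced. An analysis plan not shown may name it. All that can be said is that this text does not.
- **That the ceiling biases the comparison.** Randomisation, stratified by motor severity, makes its share similar across arms in expectation. It costs power.
- **That a known fraction is affected, or that the plan implies a particular DEUCC success rate.** Neither is printed. A Fugl-Meyer limit of 58 does not fix self-reported hand function, and the lower detectable differences fit a rate of 6-7% as well as one near 80%.
- **That this is the key secondary outcome.** The article calls the SIS hand domain and full SIS secondary, without ranking them.

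**Conclusion.** The point holds as a weakness in the definition and analysis of a secondary outcome. It is not a calculation error.

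- **Ceiling.** On a 0-100 scale, which is assumed, every participant starting above 75 must be scored a failure, and the text has no rule for them. The cost is modest if few are affected (80% to 76% at 5%) and substantial if many are (63% at 20%).
- **Dichotomising.** For a 0.40 SD effect with about 100 per arm, power drops from about 80% to about 55-61% at control success of 20-50%, under a latent-normal model. This loss exists even if nobody starts above 75.
- **Covariate.** Baseline SIS-hand is not named for the logistic model. This matters least: naming it moves power only slightly and does not remove the ceiling.

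The primary WMFT analysis and the stated power figures are untouched. The change is worth making because a clearly more sensitive analysis is available from data already collected.

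**What to change.** Before SIS data are unblinded:

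1. Prespecify an ANCOVA of the continuous 1-year SIS-hand score, adjusted for baseline SIS-hand and the stratification factors, and treat the full SIS the same way with its own baseline. Preferably this becomes the secondary test; at the least it is reported beside the 25-point rate.
2. Name baseline SIS-hand as a covariate in the logistic model for the 25-point rate.
3. Report by arm the share with baseline above 75, so that readers can judge the ceiling.

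**Cost.** No new data are needed, since the SIS is collected at baseline and 12 months. Either the responder rate becomes supportive or one more secondary analysis is reported, and the proportion-based secondary hypotheses need matching wording. The article reports that the trial is enrolling and that an interim analysis has been completed. That interim was planned for WMFT time only, but the amendment should still record that it was made without knowledge of SIS results by arm.

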**Methods/design:**

Following baseline assessment, participants are randomized by site, stratified for stroke duration and motor severity. 360 adults will be randomized, 14 to 106 days following ischemic or hemorrhagic stroke onset, with mild to moderate upper extremity impairment, recruited at sites in Atlanta, Los Angeles and Washington, D.C. The Wolf Motor Function Test (WMFT) time score is the primary outcome at 1 year post-randomization. The Stroke Impact Scale (SIS) hand domain is a secondary outcome measure.

The design includes concealed allocation during recruitment, screening and baseline, blinded outcome assessment and intention to treat analyses. Our primary hypothesis is that the improvement in log-transformed WMFT time will be greater for the ASAP than the DEUCC group. This pre-planned hypothesis will be tested at a significance level of 0.05.

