### Specific aims

#### Primary Aim and hypotheses

##### Specific Aim 1

To compare the efficacy of a fully-defined, evidence-based and theoretically defensible therapy program (ASAP) and an equivalent dose of usual and customary Occupational Therapy (DEUCC) initiated within the earliest post-acute outpatient interval (14–106 days post stroke) for significant gains in the primary outcome of paretic upper extremity function 1 year after randomization.

##### Hypothesis 1

At 1 year post randomization, the time score from the WMFT will be significantly smaller (faster) after ASAP than usual and customary occupational therapy care (DEUCC), controlled for dose.

##### Secondary hypothesis for SA 1

At 1 year post randomization, the proportion of patients with successful outcomes measured by the Stroke Impact Scale (SIS) hand domain and full SIS will be greater after ASAP than DEUCC, controlled for dose.

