##### Secondary hypothesis for SA 2A

At 1 year post randomization, the proportion of patients with successful outcomes measured by the SIS hand and full SIS will be greater after ASAP than UCC, uncontrolled for dose.

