##### Secondary hypothesis for SA 2B

At 1 year post randomization, the proportion of patients with successful outcomes measured by the SIS hand domain and full SIS will be greater after DEUCC than for UCC, uncontrolled for dose.

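### The 0.025 threshold for the comparisons with UCC covers two contrasts on one outcome only; error across WMFT time, SIS hand and full SIS is left uncontrolled, and Holm would be a better rule for the two WMFT contrasts

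*Protocol article*

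**What the plan says.** The protocol article singles out one primary test: log WMFT time at 1 year, ASAP against DEUCC. The abstract's Methods/design says of it: "This pre-planned hypothesis will be tested at a significance level of 0.05".

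The Specific aims section then lists formal secondary hypotheses.

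- **Aim 1** adds two SIS outcomes: success rates "measured by the Stroke Impact Scale (SIS) hand domain and full SIS will be greater after ASAP than DEUCC, controlled for dose".
- **Aim 2A** tests WMFT time and also that "the proportion of patients with successful outcomes measured by the SIS hand and full SIS will be greater after ASAP than UCC".
- **Aim 2B** does the same for DEUCC against UCC, with success rates "measured by the SIS hand domain and full SIS will be greater after DEUCC than for UCC, uncontrolled for dose".

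The Analysis plan gives a general threshold: "A p-value < 0.05 will be used to indicate statistical significance for all analyses". For the secondary aims it then gives a specific one. The reason stated is "Bonferroni adjustments will be made of the critical p-value for these secondary analyses, as there are two comparisons", and the rule is "ASAP to UCC and DEUCC to UCC; a p-value < 0.025 will be used to indicate significance". The divisor counts pairs of arms, not outcomes. The article states no order, gate or adjustment among WMFT time, SIS hand and full SIS, and only the treatment-by-covariate interactions are called exploratory.

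**The concern.** The article fixes a correction, a divisor and a reason for the divisor, and the reason leaves out the outcomes. Each UCC contrast carries three named hypotheses, so six tests share a correction built for two. A reader who sees p = 0.02 on one SIS outcome against UCC would reasonably take it as a result that has passed a multiplicity adjustment. It has passed one for the two contrasts on that outcome, not one for the choice among three outcomes. The two SIS hypotheses of Aim 1 fall under the general 0.05 rule with no adjustment between them.

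At stake is how secondary results may be described, above all if the primary comparison is null and attention moves to SIS or to the UCC contrasts. There is also a smaller loss: plain Bonferroni gives up power on the two WMFT contrasts that it does cover.

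**Working it through.** **Inputs from the article**

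- Threshold 0.05 in general; 0.025 for the two comparisons with UCC (Analysis plan).
- Two SIS tests in Aim 1; three outcomes × two contrasts = six tests in Aims 2A and 2B (Specific aims).
- Total sample 360; detectable effect 0.40 at 17% attrition and 0.42 at 25%, "using a two-group 2-sided t-test with a type I error of 0.05 and 80% power" (Sample size and participant accrual).

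**Assumptions**

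- Equal allocation, 120 per arm; the ratio is not stated. Two contrasts sharing the UCC arm then have correlation 0.5.
- Between-outcome correlation r is not given, so it is varied from 0 to 0.9.
- Two-sided tests, normal approximation, global null for the error rates.

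**Step 1. The plan's own figures**

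- Bonferroni: 0.05 / 2 = 0.025. Reproduced.
- Sample size: 120 × 0.83 = 99.6 per arm at 0.40 gives 80.6% power; 120 × 0.75 = 90 per arm at 0.42 gives 80.4%. Both reproduced, so equal arms and two-sided 0.05 fit the stated design.

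**Step 2. One outcome, two UCC contrasts, each at 0.025**

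- If independent: 1 − (1 − 0.025)² = 4.94%.
- With the shared UCC arm (correlation 0.5), by simulation: 4.6%.

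The correction does what its stated reason says.

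**Step 3. Adding the outcomes**

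Bounds: six tests at 0.025 cannot exceed 6 × 0.025 = 15%, and give 1 − 0.975⁶ = 14.1% if all are independent. Two tests at 0.05 cannot exceed 10%, and give 1 − 0.95² = 9.75% if independent. Simulated probability of at least one false positive:

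| Between-outcome r | Aims 2A/2B, six tests at 0.025 | Aim 1, two SIS tests at 0.05 |
|---|---|---|
| 0 | 13.3% | 9.8% |
| 0.5 | 11.9% | 9.1% |
| 0.8 | 9.4% | 7.8% |
| 0.9 | 8.0% | 7.1% |

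The Aim 1 column assumes that either SIS outcome alone counts as success. If both were required, the rate would be below 5% (0.05² = 0.25% if independent, about 3% at r = 0.9).

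**Step 4. Holm against Bonferroni for the two WMFT contrasts with UCC**

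Assume d = 0.40 for both contrasts and 100 per arm. The expected test statistic is 0.40 × √(100/2) = 2.828.

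- Bonferroni, critical value 2.241: Φ(2.828 − 2.241) = Φ(0.587) = 72% per contrast. Both significant (correlation 0.5, simulated): 58%.
- Holm (smaller p-value against 0.025, then the other against 0.05, critical value 1.960): 77% per contrast, 69% for both.

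Holm rejects whenever Bonferroni rejects. Under the global null its first step is the Bonferroni test, so the error there is the same 4.6%. In general it is held at 5%.

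**The case against.** The strongest reply is that nothing has been broken. The only overall 5% that the article states is for the primary outcome with its interim look (Interim analysis plan). The divisor is given a limited reason and meets it. A reader might infer from the 8–13% that the plan breaks a promised 5% across secondary outcomes. It makes no such promise, so that reading fails.

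A reader might also infer that an isolated SIS result would rank with a WMFT result. The text does not support this: SIS is named as a secondary outcome in Type of design, Outcome measures and the hypotheses, and Aims 2A and 2B stand under a secondary heading. The primary test is a single test and is not inflated by this issue.

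Two further limits stand. The sizes rest on a correlation that is not given. SIS hand is a subscale of the SIS, so the zero-correlation end is unrealistic for that pair. The Aim 1 hypothesis also joins the two SIS measures with a conjunction and does not say whether one suffices. Error across the other secondary outcomes and the composite cannot be sized, because their number is not shown.

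It can also be said that ordering of secondary outcomes belongs in a statistical analysis plan, and that leaving labelled secondary outcomes unadjusted is common. That is fair, and it is why gatekeeping is offered below as one of two options. It does not fully answer the point: the article itself fixes a correction and a threshold for claiming significance, without saying that the correction stops at one outcome.

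**Conclusion.** The point holds in a limited form. The 0.025 threshold controls error at about 5% across the two UCC contrasts for a single outcome. It does not control error across WMFT time, SIS hand and full SIS: about 8–13% for the six tests of Aims 2A and 2B, and about 7–10% for the two Aim 1 SIS tests if either alone counts. Both ranges assume the global null, equal arms and a between-outcome correlation from 0.9 down to 0.

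This is a matter of stating what the secondary p-values mean, not a threat to the primary conclusion. Whether to control error across secondary outcomes is a choice on which statisticians differ; leaving a reader to guess is the avoidable part. The move to Holm stands on its own merits. Error control is unaffected by the assumed effect; the size of the power gain depends on d = 0.40 for both contrasts and 100 per arm.

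**What to change.** All changes are wording in the Analysis plan; no data or patients are added.

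1. **WMFT time against UCC.** Replace Bonferroni with Holm: compare the smaller of the two p-values with 0.025 and, if it is significant, the other with 0.05. The cost is that simple matching simultaneous confidence intervals are lost.

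2. **SIS hand, full SIS, the other secondary outcomes and the composite physical domain.** Choose one of two courses and say so.
   - *Ordered testing after WMFT within each contrast.* Aim 1: WMFT time, then SIS hand, then full SIS, each at the primary level and only while the preceding test is significant. Against UCC, alpha that Holm passes to the other WMFT contrast cannot also be spent on SIS: doing both could allow up to 0.05 + 0.025 = 0.075. So either open the SIS sequences, at 0.025 per contrast, only after both WMFT contrasts are significant; or run each contrast's full sequence at 0.025 and pass its alpha on only when complete, which gives up part of the Holm gain. The cost is that a SIS result is confirmatory only if the WMFT tests before it succeed. Outcomes left outside the order are reported as supportive.
   - *No control.* State that p-values for these outcomes are not controlled across outcomes and are supportive only.

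3. **Scope.** Limit the general 0.05 sentence to the tests it is meant for, so that it does not overlap with the threshold for the secondary aims, and say whether Aim 1 needs one or both SIS outcomes.

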ICARE is a randomized controlled trial (RCT) designed to compare ASAP, an integrated set of three essential elements (skill, capacity, motivation) bundled together in a theoretically defensible and reproducible protocol, to an equivalent dose of usual and customary outpatient therapy. To date, few upper extremity rehabilitation clinical trials have included dose equivalency in the therapy application trial design. The dose-equivalent control comparison is a particularly appropriate alternative given that: 1) the EXCITE trial design and findings did not rule out the possibility that usual and customary care provided at the same dose and intensity as constraint-induced movement therapy (CIMT) would have been as efficacious, 2) findings from the VECTORS (Very Early Constraint-Induced Movement during stroke rehabilitation) trial showed that a higher intensity of CIMT applied acutely after stroke was less efficacious, while a lower intensity of CIMT yielded comparable results to a dose-equivalent usual therapy group, and 3) well-designed investigations of upper extremity rehabilitation applied in the outpatient setting that compare the effectiveness of task-specific training to that of an equivalent dose of conventional therapy are sorely lacking [28-30] with one recent exception [31]. Finally, the non-dose-equivalent, observation only group (UCC) will help determine whether ASAP or DEUCC or both are superior to current clinical practice.

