## Methods/design

We will test our hypotheses by randomizing 360 participants into a three center, single blind randomized controlled trial to investigate the effectiveness of a focused, intense, evidence-based, upper extremity rehabilitation program (ASAP) administered during the early post-acute stroke outpatient interval. Motor and quality of life measures of participants post-stroke randomized to ASAP treatment will be compared to those of participants administered an equivalent dose of usual and customary outpatient therapy (dose-equivalent usual and customary care, DEUCC), and an observation only usual and customary (UCC) occupational therapy control group. The primary study time point is 1 year after randomization. Our ultimate goal is to provide evidence to optimize post-stroke rehabilitation practice for those with mild to moderate upper limb impairments and reduce disability in the broadest sense.

All procedures conducted during this trial with human participants are carried out in compliance with federal and institutional ethical standards and in compliance with the Helsinki Declaration. All research procedures are approved by an Institutional Review Board at each of the participating sites: University of Southern California Health Sciences Campus Institutional Review Board (protocol #HS-07-00148), Emory University Institutional Review Board (protocol #IRB00001180), MedStar National Rehabilitation Hospital/MedStar Health Research Institute (protocol #2007-161), Rancho Los Amigos National Rehabilitation Center Institutional Review Board (protocol #037), Casa Colina Centers For Rehabilitation Institutional Review Board (protocol #HS-07-00148), Long Beach Memorial Care Health System Institutional Review Board (protocol #428-07), Huntington Memorial Hospital Institutional Review Board (protocol #HMH 2007–049), and Cedars-Sinai Institutional Review Board (protocol #Pro00012032).

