### Type of design

ICARE is a parallel group, three arm, single blind, phase III, superiority, randomized, controlled trial of a principle-based upper extremity training program provided in the outpatient setting after the acute hospitalization phase. Once discharged from an inpatient or acute setting and following baseline assessment, participants are randomized, no earlier than 14 days and no later than 106 days after stroke onset, to one of three intervention groups: ASAP, DEUCC or UCC. The primary outcome, collected at 1 year post-randomization, is the log WMFT time score. The secondary outcomes are the SIS hand domain subscale and the full SIS scores. To prevent unintended crossover, details of the ASAP protocol are currently embargoed; therapists who provide ASAP sign a confidentiality and nondisclosure agreement and do not provide UCC or DEUCC treatments. Outcome assessors are blinded to treatment group. The study flow is illustrated in Figure 1.

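### The two comparisons with UCC use a fixed Bonferroni threshold of 0.025; this is valid, but Holm's rule gives the same 5% control with more power at no cost in patients

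*Protocol article*

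**What the plan says.** The trial has three arms and 360 participants. Specific Aims 2A and 2B compare ASAP with UCC and DEUCC with UCC on WMFT time at 1 year. The Background says that the UCC arm "will help determine whether ASAP or DEUCC or both are superior to current clinical practice".

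The Analysis plan section sets the threshold for these aims in its last sentence. It begins "Bonferroni adjustments will be made of the critical p-value for these secondary analyses" and continues "as there are two comparisons: ASAP to UCC and DEUCC to UCC; a p-value < 0.025 will be used to indicate significance". No step-down rule, testing order or gatekeeping is named. Earlier in the same section there is a general statement: "A p-value < 0.05 will be used to indicate statistical significance for all analyses".

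The only power statement for the WMFT time score is for ASAP against DEUCC, "using a two-group 2-sided t-test with a type I error of 0.05 and 80% power". It gives detectable differences of 0.40 (17% attrition) and 0.42 (25% attrition). Nothing comparable is given for the UCC contrasts.

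**The concern.** A fixed 0.025 holds each contrast to the stricter threshold whatever the other shows. If ASAP beats UCC overwhelmingly and DEUCC against UCC gives p = 0.03, the second result is not significant. Holm's rule would declare it significant at the same family-wise error. These two contrasts are the trial's only tests of whether a 30-hour programme improves on current practice, and the Background asks about either programme or both. Showing both is where a single-step rule gives up power.

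**Working it through.** **Inputs.** Total 360 and three arms (Methods/design; Type of design). The allocation ratio is not stated; I assume 1:1:1, so 120 per arm. Attrition is 17% or 25%, the test is two-sided, and effects are in SD units (Sample size and participant accrual). The effects for the UCC contrasts are assumptions, shown as a range.

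**Reproducing the plan's figure.** With n evaluable per arm and effect δ, λ = δ√(n/2) and power ≈ Φ(λ − c), with c = 1.960 at 0.05 and 2.241 at 0.025.
- 17% attrition: n = 120 × 0.83 = 99.6; λ = 0.40 × √49.8 = 2.823; power Φ(0.863) = 80.6% (80.2% by noncentral t).
- 25% attrition: n = 90; λ = 0.42 × √45 = 2.817; power Φ(0.857) = 80.4% (80.0% by noncentral t).

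The stated 80% is reproduced, which supports 120 per arm. At 0.025 the same effects have power 72.0% and 71.8%. The effect detectable with 80% power at 0.025 (noncentral t) is 0.440 (17% attrition) or 0.463 (25%).

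**Error control of Holm.** The smaller p-value is tested at 0.025 and, if that succeeds, the larger at 0.05.
- Both nulls true: an error needs at least one p-value below 0.025, so the probability is at most 0.025 + 0.025 = 0.05.
- One null true: its p-value must be below 0.05 for an error, so the probability is at most 0.05.

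Neither step uses the dependence between the tests. With a shared UCC arm and equal n the correlation is 0.5, and the family-wise error under the global null is 4.7% for either rule. With effects 0.40 and 0, the true null is rejected 2.5% of the time under Bonferroni and 4.1% under Holm.

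**Power.** Write J(a, b) for the probability that |Z₁| > a and |Z₂| > b.
- Contrast 1 under Bonferroni: P(|Z₁| > 2.241). Holm adds J(1.960, 2.241) − J(2.241, 2.241).
- Both under Bonferroni: J(2.241, 2.241). Both under Holm: J(1.960, 2.241) + J(2.241, 1.960) − J(2.241, 2.241).

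For effects 0.40 and 0.40 with n = 100, λ = 0.40 × √50 = 2.828.
- Single contrast, Bonferroni: Φ(2.828 − 2.241) = 72.1%.
- J(2.241, 2.241) = 58.4% and J(1.960, 2.241) = 63.5%.
- Per contrast, Holm: 72.1 + (63.5 − 58.4) = 77.3% (unrounded terms).
- Both, Holm: 2 × 63.54 − 58.36 = 68.7%.
- At least one, either rule: 2 × 72.14 − 58.36 = 85.9%.

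Other cases by the same formulas, 100 per arm, Bonferroni → Holm. All but the first row keep ASAP 0.40 above DEUCC:

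| ASAP−UCC / DEUCC−UCC | ASAP contrast | DEUCC contrast |
|---|---|---|
| 0.40 / 0.40 | 72.1 → 77.3% | 72.1 → 77.3% |
| 0.50 / 0.10 | 90.2 → 90.3% | 6.4 → 10.7% |
| 0.60 / 0.20 | 97.7 → 97.8% | 20.4 → 29.3% |
| 0.70 / 0.30 | 99.7 → 99.7% | 45.2 → 56.4% |
| 0.80 / 0.40 | 100.0 → 100.0% | 72.1 → 80.7% |

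When the ASAP contrast is nearly certain, Holm in effect tests DEUCC at 0.05; at 0.80/0.40 this is Φ(2.828 − 1.960) = 80.7%.

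With 90 per arm and effects 0.40/0.40, power goes from 67.1% to 72.5% per contrast and from 52.1% to 62.9% for both. With equal effects at the extremes that the protocol cites from earlier studies (100 per arm), the gain per contrast / for both is 2.5 / 5.1 points at 0.20 and 0.6 / 1.3 points at 0.63. These are normal-approximation values; simulation agrees to about 0.1 point.

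**The case against.** Two comparisons at 0.025 each is a standard, pre-specified and valid rule. The protocol promises no power for the UCC contrasts, so no stated target is missed. That stands, and it keeps this point optional.

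A reader might infer a general loss of 5 points per contrast and 10 for both. The documents do not support that. Those figures need equal effects against UCC, which means ASAP equals DEUCC, whereas the trial is sized for ASAP to exceed DEUCC by 0.40. Under that gap Aim 2A gains almost nothing. The gain falls on Aim 2B, where power can stay low under either rule (below 30% at 0.60/0.20).

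The Analysis plan section asks whether ASAP or DEUCC is superior to UCC. For showing at least one, the two rules are identical.

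Bonferroni also has simple matching simultaneous intervals. Under Holm, a second contrast with p = 0.03 (|z| = 2.17, below 2.241) can be significant while its 97.5% interval includes zero. This is a real reporting drawback.

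Finally, Current study status reports the interim analysis done and enrolment near closing, so a looser rule needs justification. The planned interim covered only ASAP against DEUCC on WMFT time, so this is a matter of credibility, not evidence of bias.

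**Conclusion.** The point holds as an optional efficiency gain on a secondary aim. As a testing rule, Holm is never worse than the stated one and sometimes better, with the same 5% bound for the two contrasts of one outcome. That bound does not extend across the SIS or other secondary outcomes.

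The size is conditional on equal allocation, 100 evaluable per arm and assumed effects:
- Equal effects of 0.40: about 5 points per contrast and 10 for both.
- ASAP ahead of DEUCC by 0.40: about 0.1 point or less for ASAP, and 8.6 to 8.8 points for DEUCC at 0.80/0.40 and 0.60/0.20. Elsewhere in the table the DEUCC gain runs from about 4 points (0.50/0.10) to about 11 (0.70/0.30).
- Showing at least one contrast: no gain.

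It would be wrong to conclude that the plan fails to control type I error or falls short of a stated power.

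**What to change.** Replace the whole last sentence of the Analysis plan section, including its opening clause on Bonferroni adjustment, so that the two rules do not stand side by side:

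> For each outcome the two contrasts with UCC are tested by the Holm procedure: the smaller p-value against 0.025 and, if significant, the larger against 0.05; 97.5% confidence intervals are shown for both.

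In the same section, make the general statement that 0.05 applies to all analyses subject to this rule; as written, it conflicts with 0.025.

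Record the change as a dated amendment with its reason, before any unblinded comparison with UCC.

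Cost: no patients and no added family-wise error, but an amendment late in the trial and a footnote explaining that a second contrast significant under Holm may have a 97.5% interval that includes zero.
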